### Study overview

This study is a randomized, double-blind, placebo-controlled clinical trial. After baseline measurements (T0), the participants will be randomly allocated to either receive active BLT or dim red light therapy (DRLT) in a 1:1 ratio. Subsequently, they will commence their daily treatment with light, which takes place at the participants’ home for 6 weeks. After treatment, follow-up will take place at the following time points:after 6 weeks of treatment, which marks the end of treatment (T1);3 weeks after end of treatment (T2);10 weeks after end of treatment (T3);at birth (T4);2 months postpartum (T5);6 months postpartum (T6);18 months postpartum (T7).

At these time points, questionnaires, body material and information from medical files will be collected (Table 1). A flowchart of this study is shown in Fig. 3.

**Table 1 Tab1:** Overview assessment of questionnaires and collection of body material and medical files per time point

	T0	IP ^a^	T1	T2	T3	T4	T5	T6	T7
Questionnaires									
SIGH-SAD	X	X	X	X	X		X	X	X
EPDS	X	X	X	X	X		X	X	X
Life events	X	X	X	X	X		X	X	X
PSQI	X	X	X	X	X		X		
User expectations	X								
User experiences			X				X		
MABS							X		
CBCL									X
Body material									
Urine cortisol	X		X	X			X		
Saliva cortisol/melatonin	X		X	X			X		
Hair cortisol	X				X		X		
Saliva cortisol (infant)							X		
Hair cortisol (infant)							X		
Actigraphy	X ^b^				X ^c^		X ^c^		
Collecting medical files						X			

*T0* baseline (start of treatment), *T1* after 6 weeks of treatment (end of treatment), *T2 = 3* weeks after treatment, *T3 = 10* weeks after treatment, *T4* birth, *T5* 2 months postpartum, *IP* intervention period, *SIGH-SAD* Structured Interview Guide for the Hamilton Depression Scale – Seasonal Affective Disorder version, *EPDS* Edinburgh Postnatal Depression Scale, *PSQI* Pittsburgh Sleep Quality Index, *MABS* Mother and Baby Scales, *CBCL* Child Behaviour Checklist

^a^In the intervention period, the questionnaires will be assessed weekly

^b^The actiwatch needs to be worn for 8 weeks at T0

^c^At T3 and T5, the actiwatch needs to be worn for 9 days

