### Sample size

Based on previous literature [23, 41, 56], we expect a small to moderate response (time x treatment interaction on depressive symptoms). This corresponds to a 10 to 15 % reduction of depressive symptoms over the full course of treatment. To demonstrate this (with an α of 0.05 and a β of 0.80), we will need a sample size of 63 participants per arm (126 in total). To account for lost to follow up during and after treatment, we will aim at including 150 participants. Power calculations were performed using GLIMMPSE 2.1.5 software [57].

In case of withdrawal of a participant during the recruitment period, another participant will be recruited to obtain the aimed number of participants.

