### Statistical analysis

#### General

Data will be analysed using SPSS 21.0. For treatment effect analyses, we will apply an intention-to-treat procedure, since none of the participants will switch to another condition and we will include all observations of all participants until study end or withdrawal.

If necessary, skewed continuous variables will be transformed to normality prior to the analyses.

For the continuous variables and categorical variables that are assessed more than twice, we will deploy linear mixed models and generalized linear mixed models respectively. These models use all available data and account for within-subject correlation over time. They can also be used to adequately deal with possible baseline imbalances. Variables measured only once will be compared between the randomized groups using the unpaired t-test, or the Chi-Square test in case of categorical variables. All effect parameters will be supplied with a 95 % confidence interval.

Primary outcome analysis will be first crude, than adjusted. If despite randomization, prognostically important factors differ between the groups, they will be adjusted for supplemental analyses.

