#### Primary outcomes

Changes in HAM-D and EPDS rating scale scores over time will be analysed using generalized linear mixed models. Differences from baseline of HAM-D and EPDS scores at every time point will be the dependent variables, time will be the within-subject factor and treatment (BLT versus DRLT) will be the between-subjects factor.

Additional analysis will use alternative definitions of change: instead of the numerical difference of scores before and after, we will use a dichotomous response variable where improvement of ≥ 50 % to a final score ≤ 8 on HAM-D and ≤ 5 on EPDS is defined as success, otherwise not. Finally, we will perform sensitivity analysis to examine robustness of the findings with other methods using data imputation (last observation carried forward multiple imputation).

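### Last observation carried forward is a poor check on missing depression scores, and multiple imputation in its usual form would only repeat the mixed model's assumption

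*Protocol article*

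**What the plan says.** The main analysis is a mixed model for change from baseline: "Changes in HAM-D and EPDS rating scale scores over time will be analysed using generalized linear mixed models". Of these models the General part of the Statistical analysis section says "These models use all available data and account for within-subject correlation over time", and of the analysis set "we will include all observations of all participants until study end or withdrawal". It does not name the missing-data assumption, but a likelihood-based mixed model on all available data is valid under missing at random.

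On robustness the Primary outcomes part says "we will perform sensitivity analysis to examine robustness of the findings with other methods using data imputation (last observation carried forward multiple imputation". No single method has that name, so I read it as LOCF and multiple imputation. The imputation model is not described.

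Three other places bear on the point:
- **Sample size** expects a time-by-treatment interaction: "This corresponds to a 10 to 15 % reduction of depressive symptoms over the full course of treatment". It also expects attrition: "To account for lost to follow up during and after treatment, we will aim at including 150 participants".
- **Study overview, Table 1** notes "In the intervention period, the questionnaires will be assessed weekly". Both depression scales are then repeated at T1, T2, T3, T5, T6 and T7, the last at 18 months postpartum.
- **Outcome measures** says that complete follow-up will be pursued, and that EPDS and SIGH-SAD will still be collected when a woman stops or deviates from the intervention.

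**The concern.** A sensitivity analysis should change the missing-data assumption in a known direction and by a known amount, so that the reader can see how far the conclusion depends on it. The two named methods do not do this.

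LOCF sets all change after withdrawal to zero. That conflicts with a design built on scores that fall during treatment. At the postpartum visits it would put a score from pregnancy in place of one taken up to 18 months after birth. It does depart from missing at random, but the size of the departure depends on when each woman left and how steep the course was, and nobody chooses it.

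Multiple imputation in its usual form rests on the same assumption as the mixed model.

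The stake is interpretation. A gap between LOCF and the mixed model may come from LOCF alone. Agreement between multiple imputation and the mixed model may be read as robustness when it shows little. Women in a depression trial may leave because treatment is not helping or because they feel better, and neither result would say how much that matters.

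**Working it through.** **Inputs from the document.** 126 needed and 150 enrolled, so 75 per arm. The implied overall loss is 1 - 126/150 = 16%. The document does not state this rate, and the allowance covers loss both during and after treatment.

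**Assumed inputs, not in the document.** HAM-D falls linearly over 6 weeks. Every dropout has her last score at week 1, 2, 3, 4 or 5 with equal chance, regardless of her scores (completely random dropout). Between-person SD is 3 and residual SD is 3. Changes from baseline to week 6 are compared by t-test after LOCF.

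**Step 1: bias of LOCF.** The mean last week is 3, so a dropout is credited with 3/6 = 0.5 of the full fall. With fall F and loss p, the LOCF mean fall in an arm is F × (1 - 0.5p).

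*No true effect (F = 6 in both arms).* The false difference is 6 × 0.5 × (difference in loss):
- 16%/16%: 0
- 13%/19%: 3 × 0.06 = 0.18
- 8%/24%: 3 × 0.16 = 0.48

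*True effect of 3 points (F = 9 on BLT, 6 on DRLT):*
- 16% in both: 9 × 0.92 - 6 × 0.92 = 2.76
- BLT 24%, DRLT 8%: 9 × 0.88 - 6 × 0.96 = 7.92 - 5.76 = 2.16
- BLT 8%, DRLT 24%: 9 × 0.96 - 6 × 0.88 = 8.64 - 5.28 = 3.36

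Simulation agrees with these values: 2.8 with equal loss, 2.2 and 3.4 with unequal loss.

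**Step 2: rejection rate with no true effect.** Approximately Φ(-1.96 + b/SE) + Φ(-1.96 - b/SE), where b is the bias. The SE depends on where the person SD acts: about 0.855 if it is variation in slopes, about 0.72 if it is variation in level, which cancels in a change score. Simulated rejection (20,000 trials per row):

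| Fall in both arms | Loss by arm | Bias | Person SD in slope | Person SD in level |
|---|---|---|---|---|
| 6 | 16%/16% | 0.0 | 4.8% | 5.1% |
| 6 | 13%/19% | 0.18 | 5.3% | 5.5% |
| 6 | 8%/24% | 0.48 | 8.6% | 9.9% |
| 3 | 8%/24% | 0.24 | 5.9% | 6.6% |

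By the formula, 0.48/0.855 = 0.56 gives 8.7%. Other runs of the 6-point, 8%/24% case gave 8.2% to 11.0%, so 8-11% is a fair range.

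**Step 3: are the standard errors too small?** At 16%/16% loss the mean SE was 0.856 against an empirical SD of 0.850. They are about right here; the excess rejection comes from bias.

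**Step 4: does multiple imputation add information?** 400 trials of 75 per arm were simulated with assumed falls of 4.0 (DRLT) and 6.5 (BLT), comparing a likelihood estimate under missing at random (standing for the mixed model), standard multiple imputation (20 imputations) and LOCF:

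| Dropout | Full data | Mixed model | Multiple imputation | LOCF |
|---|---|---|---|---|
| At random (20% DRLT, 18% BLT) | -2.59 | -2.59 | -2.59 | -2.28 |
| Not at random (12% DRLT, 23% BLT) | -2.55 | -2.87 | -2.87 | -1.78 |

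Across trials the mixed model and multiple imputation correlated at 0.995 or more, with a mean absolute gap of about 0.06 points. In the second row both miss the full-data answer by 0.32 and agree with each other. LOCF misses it by 0.77 in the other direction. In the first row LOCF also differs from the mixed model, by 0.31, although the mixed model is right there.

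**The case against.** The strongest reply is that LOCF is not a missing-at-random method. A woman who leaves because the light is not helping keeps her poor score, and one who leaves because she feels better keeps her good score. In the non-random scenario LOCF differed from the mixed model by more than a point, so this plan would not have reported uniform agreement. That stands. A reader might infer that neither named method departs from missing at random, and the document does not support that reading. What remains is that LOCF's departure is uncontrolled: it also disagreed when the mixed model was correct, so its disagreement cannot be decoded.

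A reader might also infer that LOCF makes the standard errors too small because it treats filled-in values as observed. In the endpoint comparison checked here it did not.

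The larger rejection figure needs a threefold imbalance in loss and a steep fall in both arms. With a milder imbalance or a 3-point fall, rejection stays between about 5% and 7%. All the loss is placed in weeks 1-5, whereas the plan's allowance also covers loss after treatment. This stands too, and the size should be read as a range.

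Continued collection of both scales after the intervention is stopped answers much of the worry about women who stop because it does not help. It does not cover women who withdraw from the study.

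Finally, the imputation model may be described in an analysis plan that is not shown, so the point about multiple imputation holds only for its usual form. LOCF, by contrast, is a stated choice.

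**Conclusion.** The point holds as a cheap improvement. LOCF is named in the plan and contradicts the plan's own expectation of changing scores. It biases the treatment difference even under completely random dropout, unless the fall lost to dropout happens to be equal in the two arms. The bias can go either way, so LOCF is not reliably conservative. Its size ranges from nothing (no effect, equal loss) to about half a HAM-D point, or from 0.2 points too low to about 0.8 too low or 0.4 too high for a true 3-point effect. These figures rest on assumed linear courses, assumed loss by arm, dropout confined to the treatment weeks and an overall loss that is only implied.

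It would go too far to conclude that the primary result is biased or that the trial's type I error is raised. The primary estimate comes from the mixed model and is unaffected. The harm is confined to a robustness check that cannot be interpreted for women who withdraw from the study.

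**What to change.** In the Primary outcomes part of the Statistical analysis section, delete LOCF and state the check as follows:
- Impute HAM-D and EPDS by arm under missing at random.
- Shift the values imputed after withdrawal by a prespecified range of deltas, and report the delta at which the conclusion changes (tipping point).
- Add a reference-based version in which women who withdraw from BLT follow the DRLT profile.
- Say that the mixed model assumes missing at random, so that readers see what the deltas depart from.

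This needs no new data. It costs some wording and a few more imputation runs, and the reported range of results will look less tidy.

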#### Secondary outcomes

For saliva cortisol, areas under the curves for the morning and evening (i.e. 7 to 9 AM and 8 to 11 PM) will be calculated for subsequent analyses [23]. For saliva melatonin, areas under the curves for the evening (i.e. 8 to 11 PM) will be calculated for subsequent analyses [23].

Continuous outcomes, e.g. saliva cortisol and melatonin, will be tested with the unpaired t-test and linear mixed model. Categorical outcomes, e.g. sleep quality, will be tested with Chi-Square Test and generalized linear mixed model.

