### Saliva cortisol

As a measure of HPA-axis activity, saliva cortisol will be collected using cotton dental rolls, including 4 sequential samples at 30-min intervals starting at awakening and 3 sequential samples at hourly intervals starting 2 h before predicted bedtime with the last sample at bedtime. The samples will be collected the following day and subsequently delivered to the laboratory, where they will be centrifuged and stored at −80 °C. Samples will be analysed using a cortisol assay on an immunoanalyser system. For determination of the diurnal time course of saliva cortisol levels, only days with at least 6 valid samples will be included in analyses.

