### Saliva melatonin

As a measure of a participant’s circadian phase position, saliva melatonin levels will be collected using cotton dental rolls at hourly intervals with 3 sequential samples, starting 2 h before predicted bedtime with the last sample at bedtime, under dim light conditions. One sample will be taken at awakening. The samples will be collected the following day and subsequently delivered to the laboratory, where they will be centrifuged and stored at −80 °C. All samples will be analysed using Liquid Chromatography Tandem Mass Spectrometry (LC-MS/MS). For determination of a rise in melatonin levels in het evening, only days with 3 valid evening samples will be included in the analyses [23].

The Dim Light Melatonin Onset (DLMO; the time point when melatonin secretion rises over a predefined threshold in the evening [66]) will be calculated after measuring the melatonin evening curve. The DLMO is a reliable estimate of circadian phase position [66].

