### Infant stress response

To measure the infant stress response, we will collect saliva cortisol before and 15, 30 and 45 min after a routine vaccination at T5. We will use the same procedures and analyses as with the mothers.

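### Saliva cortisol and melatonin AUCs are defined on fixed clock windows that samples timed to awakening and bedtime can never fill

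*Protocol article*

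**What the plan says.** The statistical section on secondary outcomes defines the cortisol summaries by clock time: "areas under the curves for the morning and evening (i.e. 7 to 9 AM and 8 to 11 PM) will be calculated". For melatonin it says: "For saliva melatonin, areas under the curves for the evening (i.e. 8 to 11 PM) will be calculated".

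The measurement sections time collection differently. Under Saliva cortisol, the morning set is described as "including 4 sequential samples at 30-min intervals starting at awakening" and the evening set as "3 sequential samples at hourly intervals starting 2 h before predicted bedtime with the last sample at bedtime". Under Saliva melatonin, the evening samples are taken "at hourly intervals with 3 sequential samples, starting 2 h before predicted bedtime with the last sample at bedtime".

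The Background section on BLT and depression says that BLT shifts the circadian rhythm. The Hypotheses section expects improved sleep patterns alongside clinical improvement.

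For infants, the section on the stress response states: "we will collect saliva cortisol before and 15, 30 and 45 min after a routine vaccination at T5". It then carries the mothers' procedures and analyses over to the infants without naming an exception.

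**The concern.** The article fixes both how the saliva is collected and how it is summarised, and the two do not fit. The windows are tied to the clock and the samples to each woman's awakening and bedtime. Both windows are also longer than the time sampled.

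The article does not say what happens to samples outside a window or to the unsampled part of it. There are three ways to proceed:

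- use every sample and ignore the clock times;
- cut the curve at the window edges;
- fill the gaps.

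These give different numbers, and the choice could end up being made after the data are seen.

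The coverage of each window is set by sleep timing, which the treatment is expected to influence. If the curve is cut at the window edges or the gaps are filled, the arms could differ in AUC partly because they differ in timing or coverage. These AUCs are the stated saliva summaries for the secondary hypothesis on cortisol and melatonin.

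**Working it through.** **Inputs from the protocol article.** Morning cortisol: 4 samples, 30 min apart, from awakening. Evening cortisol and melatonin: 3 samples, 60 min apart, the last at bedtime. Windows: 7–9 AM (120 min) and 8–11 PM (180 min).

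**Sampled span** = (number of samples − 1) × interval.

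- Morning: (4 − 1) × 30 = 90 min, against a window of 120 min.
- Evening: (3 − 1) × 60 = 120 min, against a window of 180 min.

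**Upper limit on coverage** = span ÷ window.

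- Morning: 90 ÷ 120 = 75%.
- Evening: 120 ÷ 180 = 67%.

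These limits need no assumption about when anyone sleeps.

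**Coverage by sleep timing** = max(0, min(last sample, window end) − max(first sample, window start)) ÷ window length. The wake times and bedtimes below are assumptions, since the article gives none.

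| Awakening | Samples in 7–9 AM | Minutes covered | Coverage |
|---|---|---|---|
| 5:30 | 1 | 0 | 0% |
| 6:00 | 2 | 30 | 25% |
| 6:30 | 3 | 60 | 50% |
| 7:00 to 7:30 | 4 | 90 | 75% |
| 8:00 | 3 | 60 | 50% |
| 8:30 | 2 | 30 | 25% |
| 9:00 | 1 | 0 | 0% |

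| Bedtime | Samples in 8–11 PM | Minutes covered | Coverage |
|---|---|---|---|
| 21:00 | 2 | 60 | 33% |
| 21:30 | 2 | 90 | 50% |
| 22:00 to 23:00 | 3 | 120 | 67% |
| 23:30 | 2 | 90 | 50% |
| 24:00 | 2 | 60 | 33% |
| 01:00 | 1 | 0 | 0% |

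All morning samples fall inside the window only for awakening between 7:00 and 7:30, and all evening samples only for bedtime between 22:00 and 23:00.

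**Illustration of the timing effect.** Suppose awakening moves from 7:00 to 6:00 (an assumed shift; the article gives no size). Morning coverage falls from 90 to 30 min. If the curve were cut at the window edges and the concentration were flat at c, the AUC would fall from 90c to 30c, to one third, with no change in concentration. This shows how the problem would arise; it does not predict its size.

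**Infants.** One sample before and three after vaccination make 4, spread over 45 min. The maternal scheme has 4 + 3 = 7 samples, and its validity rule reads "only days with at least 6 valid samples will be included in analyses". Neither that rule nor a morning or evening AUC suits a 45-minute response curve.

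**The case against.** The clock times may be no more than labels for the morning and evening sample sets, borrowed from the study cited beside them. All samples would then be used, and nothing would be cut or filled. That is possible, but the abbreviation i.e. introduces the times as a definition, and as labels they still have the wrong length. A reader might infer that the AUCs will be extrapolated to fill the windows. The article does not say so; it is one possible handling among several.

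The timing argument also has limits. The Outcome measures section only lists sleep and rhythm measures and predicts nothing; the expectation of a timing effect comes from the Background and the Hypotheses. Shift workers are excluded, which makes extreme times less typical, and chronotype is a potential covariate. For melatonin, an earlier evening rise is itself a hormonal effect, so a difference due to timing is not simply an artefact. Urinary and hair cortisol and DLMO do not depend on these windows. All of this stands and limits the consequence, but it does not remove the mismatch.

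A stronger reading is tempting for infants: that the six-sample rule would exclude every one of them, or that their stress response cannot be analysed. The article does not support this. The Saliva cortisol section ties that rule to the diurnal time course, which a vaccination test is not. The carry-over sentence can be read as covering collection and assay, and it appears again for infant hair. The general statistical section also provides linear mixed models for continuous variables assessed more than twice, which four infant samples can satisfy. What remains is a loosely worded sentence.

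**Conclusion.** The point holds for the maternal saliva AUCs. The defined windows exceed the sampled spans by 30 min in the morning (120 − 90) and 60 min in the evening (180 − 120), so at most 75% and 67% can be covered for any woman. This follows from the article's own schedule. It is a conflict between two stated rules, not detail left to a fuller document.

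An arm difference in a clock-window AUC could partly reflect timing or coverage. That rests on two conditions: BLT does move wake times or bedtimes, and the windows are applied as written. The size is unknown without the actual sleep times.

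The infant wording is a minor matter of clarity. Only secondary outcomes are concerned; the primary analysis of HAM-D and EPDS is untouched. The change should be made, and it is cheap.

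**What to change.** In the statistical section on secondary outcomes, replace the clock windows with the sampled intervals and compute the AUCs from recorded sample times:

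- morning cortisol: from awakening to 90 min after it;
- evening cortisol and melatonin: from 2 h before bedtime to bedtime.

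A complete sample set then covers its interval for every woman. If the clock times were only labels, delete them.

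This has one small downside. If melatonin and bedtime both move earlier, a bedtime-anchored AUC can hide the phase shift. Evening melatonin should therefore be read together with DLMO, which the article already plans as the measure of circadian phase.

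In the section on the infant stress response, add a sentence saying that the maternal six-sample diurnal rule and the morning and evening AUCs do not apply to the four vaccination samples.

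The cost is analysis wording only; sampling, visits and assays stay as they are.

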**Methods:**

In this study, 150 pregnant women (12–18 weeks pregnant) with a DSM-V diagnosis of depressive disorder will be randomly allocated in a 1:1 ratio to one of the two treatment arms: treatment with BLT (9.000 lux) or treatment with dim red light therapy (100 lux). Both groups will be treated for 6 weeks at home on a daily basis for 30 min, within 30 min of habitual wake-up time. Follow-up will take place after 6 weeks of therapy, 3 and 10 weeks after end of therapy, at birth and 2, 6 and 18 months postpartum. Primary outcome will be the average change in depressive symptoms between the two groups, as measured by the Structured Interview Guide for the Hamilton Depression Scale – Seasonal Affective Disorder version and the Edinburg Postnatal Depression Scale. Changes in rating scale scores of these questionnaires over time will be analysed using generalized linear mixed models. Secondary outcomes will be the changes in maternal cortisol and melatonin levels, in maternal sleep quality and gestational age, birth weight, infant behaviour, infant cortisol exposure and infant cortisol stress response.

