### Aims

In this study, we will primarily study the effects of BLT on depression during pregnancy, including adverse effects. Second, we will study whether this clinical improvement is accompanied by improved sleep quality and normalized melatonin and cortisol levels during pregnancy. Third, we will study the effects of BLT on gestational age, birth weight, infant behaviour, infant cortisol stress response and long-term cortisol exposure of the infant.

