### Outcome measures

The primary outcome measure will be the average change in depressive symptoms between the two groups, as measured by the Structured Interview Guide for the Hamilton Depression Scale – Seasonal Affective Disorder version (SIGH-SAD) and the EPDS at different time points. Second, we will study responders vs. non-responders, where response is defined as a ≥50 % decrease to a final score of ≤ 8 on the 17-item Hamilton scale and ≤ 5 on the EPDS.

The secondary outcome measures of this study will be the changes in maternal cortisol and melatonin levels (1), in maternal circadian rhythm (2) and in birth and child outcomes (3).Morning and evening cortisol levels in saliva will be measured as a measure for HPA-axis activity. Morning and evening melatonin levels in saliva will be measured as measure of a participant’s circadian phase position. Outcome measures will be the changes in cortisol and melatonin saliva levels between the two groups.Total 24-h cortisol excretion will be determined from urine. Outcome measure will be the changes in cortisol levels within and between the two groups.Hair will be used as a long-term measure for cortisol excretion. Changes in levels between the two groups will be used as outcome measure.Through actiwatches and a structured questionnaire (the Pittsburgh Sleep Quality Index – PSQI), information will be obtained regarding total sleep time, sleep efficiency and sleep onset latency, as well as circadian estimates from the rest activity rhythm such as intradaily and interdaily variability and rhythm amplitude.Differences in birth and child outcomes between the two groups will be used as outcome measures: pregnancy duration, birth weight, child behaviour, long-term cortisol exposure and cortisol stress response at a routine vaccination.

Finally, we will ask about user expectations and user experiences.

Complete follow-up will be pursued. In case of discontinuing or deviating from the intervention, we will collect outcomes of EPDS and SIGH-SAD assessment.

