### PSQI

The PSQI, a structured 19-item self-questionnaire with 5 additional items reported by bedpartner, assesses sleep quality, including a wide variety of factors, such as sleep duration and latency [69]. The sum score ranges from 0 to 21 points, with higher values corresponding to lower sleep quality [69]. These 19 items generate 7 component scores: subjective sleep quality, sleep latency, sleep duration, habitual sleep efficiency, sleep disturbances, use of sleeping medication and daytime dysfunction [69].

A cut-off of 5 will be applied, where a score of <5 indicates poor sleep and ≥5 indicates good sleep [69]. The PSQI has a sensitivity of 89.6 % and a specificity of 86.5 % [69].

The PSQI will be assessed on a monthly base and weekly in the intervention period.

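### The only analysis named for PSQI sleep quality is categorical, which discards information from a 0–21 score measured repeatedly

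*Protocol article*

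**What the plan says.** The abstract (Methods) states: "Secondary outcomes will be the changes in maternal cortisol and melatonin levels, in maternal sleep quality". The Aims ask whether clinical improvement is "accompanied by improved sleep quality and normalized melatonin and cortisol levels during pregnancy". Neither place names a scale for the change.

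The PSQI section describes a numerical measure: "The sum score ranges from 0 to 21 points, with higher values corresponding to lower sleep quality". It then adds a dichotomy: "A cut-off of 5 will be applied, where a score of <5 indicates poor sleep and ≥5 indicates good sleep". It also sets repeated measurement: "The PSQI will be assessed on a monthly base and weekly in the intervention period". Table 1 marks the PSQI at T0, in the intervention period, and at T1, T2, T3 and T5.

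Under Statistical analysis, Secondary outcomes, sleep quality is the example of a categorical outcome: "Categorical outcomes, e.g. sleep quality, will be tested with Chi-Square Test and generalized linear mixed model". The examples of continuous outcomes there are salivary cortisol and melatonin. The General subsection assigns linear mixed models to continuous variables, and generalized linear mixed models to categorical ones, when they are assessed more than twice. It assigns the Chi-square test to categorical variables measured once.

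**The concern.** The interest is in how far sleep quality improves, but the only named analysis sees whether a woman is on one side of a threshold. A woman whose score goes from 14 to 7 has halved it, yet she is above 5 both times and counts as unchanged. Any movement that does not cross the cut contributes nothing.

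The protocol treats its primary scales differently. Under Primary outcomes, numerical differences from baseline in HAM-D and EPDS come first, and the dichotomous response is an additional analysis. Sleep quality gets only the category, with no reason given. At stake is the precision of the PSQI comparison, which is one part of the secondary hypothesis on sleep, cortisol and melatonin.

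**Working it through.** **The plan's own figure.** The article gives no effect size, SD, good/poor split or power for sleep quality. Its 63 per arm is for the primary depression outcome. A two-sided 5% test with 80% power and a difference of 0.5 SD needs n = 2 × (1.960 + 0.842)² / 0.5² = 62.8, so 63 per arm. This matches the stated number, but 0.5 SD is an assumption made here. The article gives no standardised effect for its calculation, so this does not reproduce it.

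**Loss of information from a cut.** For a normal score cut so that a fraction q falls on one side, the dichotomy's efficiency relative to the score is φ(z_q)² / [q(1 − q)].

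- 50/50: 0.399² / 0.25 = 0.637, a loss of 36%
- 70/30: 0.348² / 0.21 = 0.576, a loss of 42%
- 80/20: 0.280² / 0.16 = 0.490, a loss of 51%
- 90/10: 0.1755² / 0.09 = 0.342, a loss of 66%

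**Power at one time point.** Inputs: 63 per arm (Sample size section); two-sided 5%, normal score and d = 0.5 SD (all assumed).

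For the score, power = Φ(0.5 × √(63/2) − 1.960) = Φ(0.846) = 80%.

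For the dichotomy, the two arms' proportions are Φ values 0.5 SD apart, averaging q. They are compared with the usual two-proportion formula (pooled variance under the null, unpooled under the alternative). At 50/50 the proportions are 0.599 and 0.401. The critical difference is 1.960 × √(2 × 0.25/63) = 0.175 and the standard error is √(2 × 0.599 × 0.401/63) = 0.087. Power is therefore Φ((0.197 − 0.175)/0.087), about 60%.

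| Split | Proportions | Power, score | Power, category | n per arm for 80%, category (score: 63) |
|---|---|---|---|---|
| 50/50 | 0.599 / 0.401 | 80% | 60% | 100 |
| 70/30 | 0.786 / 0.614 | 80% | 55% | 112 |
| 80/20 | 0.868 / 0.732 | 80% | 48% | 134 |
| 90/10 | 0.942 / 0.858 | 80% | 35% | 200 |

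**Sensitivity to the effect.** With d = 0.3 and 63 per arm, the score has 39% power and the category 27%, 21% and 16% at 50/50, 80/20 and 90/10. Over d = 0.3 to 0.5, 63 or 75 per arm, and splits from 50/50 to 80/20, the relative loss of power runs from 21% to 46%. At 90/10 it is 54% to 60%.

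**What this does not cover.** The comparison is for one time point. A generalized linear mixed model uses the repeated assessments and their within-woman correlation, but it still sees only the category. Its exact loss is not computed here.

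**The case against.** The strongest reply is that the sleep hypothesis does not rest on the PSQI category. The Outcome measures and Actigraphy sections list total sleep time, sleep efficiency, sleep onset latency and rest-activity measures, which are continuous. This stands. A reader might infer that a true sleep benefit would be reported as none; the article does not support that.

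A reader might also infer that the article contradicts itself, defining the outcome as change on the 0–21 score in one place and as a category in another. It does not. No section ties the change to the sum score, the PSQI section itself introduces the cut-off, and a change of category over time is still a change that a generalized linear mixed model can describe. What remains is an inefficient choice.

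Nor can a fixed share of power be said to be lost. The range of a third to a half describes effective sample size for splits between about 50/50 and 80/20. At d = 0.5 and an even split, power falls by a quarter in relative terms (80% to 60%). One might suppose that most of these women lie far from the cut, because the Background says sleep is typically disturbed in pregnancy, but no PSQI distribution is given.

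Finally, the General subsection already sends repeated continuous variables to linear mixed models, and the form of a secondary endpoint may be left to an analysis plan. That answer is only partial: the article does make a choice for sleep quality, and that choice is categorical.

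**Conclusion.** The point holds as one of analysis choice for one secondary outcome. Followed as written, the PSQI comparison would lose about 36% of its effective sample size at an even split, about half at 80/20 and about two thirds at 90/10. With 0.5 SD and 63 per arm, power falls from 80% to about 60%, 48% and 35% respectively.

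These figures assume a normal score, a single time point and a two-sided 5% test. The effect and the splits are also assumptions, and reading the category as the cut-off of 5 is the most plausible interpretation. The trial was not sized for sleep quality, so no stated power claim fails. The primary analysis and the actigraphy outcomes are unaffected. The change is worth making because it recovers information at almost no cost.

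**What to change.** In Statistical analysis, Secondary outcomes, state that the PSQI sum score (0–21) is analysed as a continuous outcome with the linear mixed model already prescribed in the General subsection, accounting for the T0 score. Keep the proportions of good and poor sleepers as supportive or descriptive, and remove sleep quality as the example of a categorical outcome. This also removes the use of a Chi-square test for a variable measured repeatedly, which the General subsection does not provide for.

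If the category is kept, its labels must first be reconciled with the scale, since the PSQI section calls low scores poor sleep while stating that higher scores mean lower quality. That is a separate correction.

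The cost is about one sentence. The data are already planned, and neither the sample size nor the schedule changes.
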